# The added value of a mobile application of Community Case Management on referral, re-consultation and hospitalization rates of children aged under 5 years in two districts in Northern Malawi: study protocol for a pragmatic, stepped-wedge cluster-randomized controlled trial

**DOI:** 10.1186/s13063-017-2213-z

**Published:** 2017-10-11

**Keywords:** Integrated management for childhood illness (IMCI), Community health workers, Child health, Infectious diseases, mHealth, Malawi

## Abstract

**Background:**

There is evidence to suggest that frontline community health workers in Malawi are under-referring children to higher-level facilities. Integrating a digitized version of paper-based methods of Community Case Management (CCM) could strengthen delivery, increasing urgent referral rates and preventing unnecessary re-consultations and hospital admissions. This trial aims to evaluate the added value of the Supporting LIFE electronic Community Case Management Application (SL eCCM App) compared to paper-based CCM on urgent referral, re-consultation and hospitalization rates, in two districts in Northern Malawi.

**Methods/design:**

This is a pragmatic, stepped-wedge cluster-randomized trial assessing the added value of the SL eCCM App on urgent referral, re-consultation and hospitalization rates of children aged 2 months and older to up to 5 years, within 7 days of the index visit. One hundred and two health surveillance assistants (HSAs) were stratified into six clusters based on geographical location, and clusters randomized to the timing of crossover to the intervention using simple, computer-generated randomization. Training workshops were conducted prior to the control (paper-CCM) and intervention (paper-CCM + SL eCCM App) in assigned clusters. Neither participants nor study personnel were blinded to allocation. Outcome measures were determined by abstraction of clinical data from patient records 2 weeks after recruitment. A nested qualitative study explored perceptions of adherence to urgent referral recommendations and a cost evaluation determined the financial and time-related costs to caregivers of subsequent health care utilization. The trial was conducted between July 2016 and February 2017.

**Discussion:**

This is the first large-scale trial evaluating the value of adding a mobile application of CCM to the assessment of children aged under 5 years. The trial will generate evidence on the potential use of mobile health for CCM in Malawi, and more widely in other low- and middle-income countries.

**Trial registration:**

ClinicalTrials.gov, ID: NCT02763345. Registered on 3 May 2016.

**Electronic supplementary material:**

The online version of this article (doi:10.1186/s13063-017-2213-z) contains supplementary material, which is available to authorized users.

## Background

Community Case Management (CCM) is a derivative of the paper-based Integrated Management for Childhood Illness (IMCI) clinical algorithm. The strategy was developed by the World Health Organization (WHO) and United Nations Children’s Fund (UNICEF) to reduce the burden of morbidity and mortality from leading causes of disease (i.e., pneumonia, malaria and diarrhea) among children aged under 5 years in low- and middle-income countries (LMICs) [1–3]. CCM is a widely used intervention for children aged under 5 years and is deployed at village clinics by the largest cadre of community health workers (CHWs) in Malawi, known as health surveillance assistants (HSAs) [4].

Using a stepwise approach, CHWs are guided through a “Sick Child Form,” constituting a series of standardized questions and assessment items to direct clinical management [5]. Depending on the manifestation of “sick” and “danger” signs, which are recorded by hand in a village clinic register, children are given medicine or managed at home. Those children who are severely unwell and outside the scope of CHWs’ practice [6] are urgently referred to the nearest higher-level health facility for more comprehensive clinical management (which can be primary- or secondary-care facilities including health centers, community/rural or district hospitals), with advice given to caregivers about the reason for the referral and the location of the nearest facility [7].

Correct identification of children requiring urgent referral is largely dependent upon CHWs’ fidelity to CCM guidelines, which has been frequently reported as suboptimal [3, 7–10]. Poor completion of relevant CCM assessment items may hinder early recognition of serious illness, reducing urgent referrals to higher-level facilities. Information about CCM-directed urgent referral rates in Malawi is limited. However, assessment of the quality of implementation of the CCM program after national scale-up in 2008 reported that CHWs on average made two urgent referrals (per 1000 children) each month [11]. Given the countries’ annual childhood mortality rates from pneumonia (23%), malaria (14%) and diarrhea (18%) [12], this suggests that many children meeting the classification for urgent referral are not being identified. Under-referral risks repeat consultations [13] for the same illness episode as well as hospitalization of those children with serious illness who are left untreated. But, due to the lack of an integrated and electronic medical record system [14, 15], it is unclear which children are brought back to village clinics because they are still unwell, and which of those admitted to hospital were urgently referred by CHWs at the index visit.

Of equal importance is that children who are urgently referred are actually taken to higher-level facilities (in other words, that the referral is completed) when advised [16, 17]. Failure to follow recommendations risks the development of chronic conditions or acute complications [18]. It is suggested that over 50% of caregivers in sub-Saharan Africa whose children are urgently referred, do not take their child for onward care [16, 19–21]. Prohibitive financial and time-related costs incurred by caregivers travelling large geographical distances to facilities [22], and mistrust in CHW “diagnoses” and treatment decisions [23, 24] have been cited as factors contributing to poor referral completion rates.

Utilizing mobile health (mHealth) technologies (e.g., smartphones, tablets) to deliver CCM could encourage the dispensation of more appropriate treatment recommendations [25] thereby increasing urgent referral rates. Potential improvements may be underpinned by a combination of better control of how the end-user navigates through assessment questions (e.g., built-in validation rules forcing completion of relevant fields with valid data before advancing to the next field/screen) [26]; enhanced CHW motivation linked to the prestige of using advanced technology in a predominantly paper-based health care system; automated presentation of the next-steps reducing reliance on memory [27], and heightened perceived efficacy and caregiver trust in CHWs’ decisions linked to clearer explanations about the child’s condition and recommended treatment [27].

Despite the opportunities that mHealth may afford for circumventing some of the limitations of current paper-based delivery [26], there is a paucity of evidence demonstrating the comparative benefits of deploying digitized versions of CCM on health service utilization and associated patient costs. To address this evidence gap in a pragmatic cluster-randomized trial, we will evaluate the added value of an electronic CCM App (truncated to SL eCCM App) developed as part of the Supporting Low-cost Interventions For disEase control (Supporting LIFE) program. As well as contributing to the broader mHealth literature, we anticipate that trial findings will provide Malawi’s mHealth Working Group with empirical data, which can be used to inform policy regarding the opportunities to Malawi of introducing such interventions for CCM. Our hypothesis is that adding the SL eCCM App to sick child assessments will increase urgent referral rates and reduce re-consultation and hospitalization rates.

The main objectives of this trial were to determine the:▪ Added value of the SL eCCM App (used with paper-CCM) on referral, re-consultations and hospitalization rates among acutely unwell children aged under 5 years, compared with paper-CCM alone▪ Factors influencing caregivers’ decisions to comply with urgent referral recommendations▪ Direct and indirect costs to caregivers presenting to higher-level facilities and/or re-attending village clinics after the index visit when using paper-CCM and the paper-CCM + SL eCCM App

### Previous work justifying this trial

To address repeated calls for bridging the evidence gap regarding mHealth interventions in LMICs [28–30], the Supporting LIFE study team, which consisted of health information systems (HIS) researchers, physicians, epidemiologists and clinical researchers from Imperial College London (ICL), University College Cork (UCC), University of Washington (USA), Lund Universitet (Sweden), Mzuzu University, Luke International (LIN) and the College of Medicine (Malawi), purposely developed the SL eCCM App [31]. Despite CCM being one of the most ubiquitous child health interventions available in LMICs, there have been few attempts to evaluate digitized versions of these guidelines beyond pilot and feasibility studies. Given the variable standards with which CCM is delivered by CHWs, there is a need to identify alternative solutions to enhance quality of health care delivery in the community.

The Supporting LIFE study team conducted a feasibility study between July and September 2015 which explored the acceptability and usability of the SL eCCM App among HSAs in Malawi and the study procedures proposed as part of this trial (the feasibility study, including findings are described in [15] or are forthcoming elsewhere). This trial builds on this previous work.

## Methods/design

### Trial design

This is a pragmatic, stepped-wedge cluster-randomized trial assessing the added value of the SL eCCM App (used with paper-CCM) on referral, re-consultation and hospitalization rates of children aged under 5 years, within 7 days of the index visit. This design was chosen due to insufficient human resources to deliver the intervention to all clusters simultaneously [32] and local advice that withholding the intervention to some clusters may negatively affect participation. We aimed to recruit 102 HSAs and collect data on 8000 children from village clinics across two districts in Northern Malawi between July 2016 and February 2017. HSAs were grouped into six geographic-based clusters. Training workshops were conducted prior to the control (paper-CCM) and intervention (paper-CCM + SL eCCM App) in assigned clusters. Clusters were randomly assigned to the timing of crossover from the control to the intervention [32] for covariate equipoise between phases [33]. A nested qualitative study explored HSA and caregiver perceptions of caregiver adherence to urgent referral recommendations; a cost evaluation investigated the financial and time-related costs to caregivers of seeking subsequent health care for their child after the index visit. Figure 1 shows the trial flow chart; Fig. 2 the trial design (before randomization) and Fig. 3 the Standard Protocol Items: Recommendations for Interventional Trials (SPIRIT) Figure. This protocol adheres to the SPIRIT 2013 Statement for clinical trial protocols (Additional file 1) [34].

**Fig. 1 Fig1:**
[figure not shown]
Trial flow diagram

**Fig. 2 Fig2:**
[figure not shown]
Trial design

**Fig. 3 Fig3:**
[figure not shown]
Standard Protocol Items: Recommendations for Interventional Trials (SPIRIT) Figure

## Methods

### Study setting

Malawi is a land-locked country in central southern sub-Saharan Africa [35]. It is one of the poorest nations in the world, ranked 160th out of 182 on the Human Development Index [36]. Although 68% of health care services are government subsidized [18], physical access is limited and inequitable, with only 54% population residing within 5 km of the nearest health facility [37]. Although English has been the official language of Malawi since Independence in 1964 the majority of the population have limited proficiency. Chichewa is the language spoken in Nkhata Bay and Tonga and Tumbuka are spoken in Rumphi District; all of which were provisioned for in this trial. HSAs are posted to hard-to-reach locations where they deliver a mixture of preventative and curative community health programs to a catchment area of approximately 1000 people [4]. They receive 6 days of initial CCM training [5, 6, 11] before implementing CCM to children aged under 5 years from village clinics (operated by one HSA). Village clinics are equipped with rudimentary job aids, which typically include the paper-CCM decision pro forma in English (referred to as the Sick Child Form), a village clinic register for recording patient visits [5], a stopwatch for measuring respiratory rate (RR), and access to basic medications.

### Eligibility criteria

#### Inclusion criteria

Participants were eligible to be included in the trial if they fulfilled the following criteria:

##### Health surveillance assistants

▪ Completion of the Ministry of Health’s (MoH’s) 6-day CCM training program▪ Fluent in spoken and written Chichewa, Tonga or Tumbuka (± English)▪ Attendance at both training workshops▪ Voluntary written consent

##### Caregivers

▪ Caregivers are aged 18 years and older▪ Caregivers with spoken fluency in Chichewa, Tonga or Tumbuka (it is not anticipated that many will speak English)▪ Child is aged 2 months or older and up to 5 years▪ Voluntary verbal consent

#### Exclusion criteria

Participants fulfilling any of the following criteria were not eligible to take part in this trial:

##### Health surveillance assistants

▪ Unable/unwilling to attend both training workshops▪ Unable/decline voluntary written consent

##### Caregivers

▪ Caregiver is aged below 18 years▪ Child is aged below 2 months or 5 years and older▪ Child is convulsing, unconscious or unresponsive at presentation▪ Unable/unwilling to give voluntary verbal consent

### The Supporting LIFE electronic Community Case Management Application

SL eCCM App is a smartphone App developed for Android OS 3.0 Honeycomb or above; the smartphone selected to run the App for this trial was the HTC Desire 526G. The App is in English and replicates the paper-based CCM decision aid (i.e., the Sick Child Form) in terms of wording and order of presentation of assessment questions (Fig. 4). Patient data is entered via a touch-sensitive dynamic interface. Field validation forced HSAs to complete all required fields prompted by the App’s decision rule and within clinically valid parameters. Current configuration of the SL eCCM App only permits data entry and so previously entered records cannot be retrieved. Included in the App is a countdown tap-screen feature for measuring RR. The number of screen taps within 60 s equates to a child’s RR. Whilst 60 s was the default measurement period for the trial, the App permits the user to select shorter periods (i.e., 15, 30 and 45 s), where a RR equivalent of 60 s is calculated from the time intervals between taps. HSAs were encouraged to use this feature, but could elect to use the stopwatch (as per standard practice). The SL eCCM App uses RESTful web services communicating over JSON to a Cloud-based web server, running on an Amazon Elastic Compute Tomcat instance. The web-server comprises a middle-tier Spring Model-View Controller framework and uses Java Persistence API to communicate to a back-end MySQL database running on an Amazon Relation Database Service instance. My SQL database (referred to as the SL central database) is supported by Amazon Web Services (AWS) Cloud data storage solutions, and has been created to store uploaded patient data from the SL eCCM App (Fig. 5). Patient data is uploaded onto the SL central database when the App is physically synced with the central database. The robustness and fidelity of the App’s clinical algorithm to paper-CCM was tested iteratively over the 4 years of development against a suite of automated tests. It also underwent additional manual checks by members of the study team (which includes a family physician), by creating artificial clinical scenarios and cross-referencing the logic with the Sick Child Form), as well as with 12 HSAs in a feasibility study conducted in Malawi between July and September 2015 [15].

**Fig. 4 Fig4:**
[figure not shown]
Screenshots of the Supporting LIFE electronic Community Case Management Application (SL eCCM App)

**Fig. 5 Fig5:**
[figure not shown]
System architecture supporting the Supporting LIFE electronic Community Case Management Application (SL eCCM App)

### Outcome measures

#### Main outcomes

▪ Urgent referrals to higher-level facilities in the 7 days following the index visit, ascertained from abstraction of patient records 2 weeks after the index visit.*◦ Caregiver-completed referrals in the 7 days following the index visit, determined from abstraction of patient records (i.e., caregivers who were urgently referred and who presented)◦ Caregiver self-referrals to primary or secondary health facilities (i.e., parents/caregivers of children not urgently referred at the index visit, but who presented anyway)
▪ Re-consultations at village clinics due to deterioration of illness, and hospitalizations in the 7 days following the index visit ascertained from abstraction of patient records 2 weeks after the index visit

*Primary outcome measure used to determine the number of participants needed to power the trial.

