## Discussion

To the authors’ knowledge the Supporting LIFE trial is the first large-scale trial evaluating the added value of an electronic version of CCM compared to paper-CCM alone. This trial will provide important data regarding the impact of digitizing CCM on HSA urgent referral practices and factors influencing health service utilization in Malawi. The outcome of referral rate provides a proxy quality indicator: higher urgent referral rates and reduced re-consultation and hospitalization rates compared to paper-CCM may suggest that integrating digitized versions of CCM to the clinical workup improves standards of CCM delivery. Our findings may also be used by the mHealth Working Group in Malawi and decision-makers in other LMICs to better determine the benefit to health care of introducing similar mHealth CCM tools. More broadly, this trial is expected to inform the design and conduct of future evaluations of mHealth technologies for CCM.

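### Village-clinic re-consultation and self-referral can fall because a referral moves or relabels a visit, so a fall in the village-clinic count alone cannot show that re-consultation was prevented

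*Protocol article*

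**What the plan says.** Under Outcome measures, Main outcomes, the protocol article divides presentations at higher-level facilities by what the health surveillance assistant (HSA) decided at the index visit:

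- Completed referral: "i.e., caregivers who were urgently referred and who presented".
- Self-referral: "Caregiver self-referrals to primary or secondary health facilities (i.e., parents/caregivers of children not urgently referred at the index visit, but who presented anyway".

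The other main outcomes are "Re-consultations at village clinics due to deterioration of illness, and hospitalizations in the 7 days following the index visit". Re-consultation is thus tied to one type of site. Hospitalization is tied neither to village clinics nor to the referral decision.

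The Background states the hypothesis that the App "will increase urgent referral rates and reduce re-consultation and hospitalization rates". The Discussion says that "higher urgent referral rates and reduced re-consultation and hospitalization rates compared to paper-CCM may suggest that integrating digitized versions of CCM" improves delivery. Neither section gives a direction for self-referral.

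The Sample size section assumes a 1% urgent referral rate in control and 7–8% with the App, 4000 children in each phase, and 260 under-referred children in control. The Background reports that more than half of referred children in the region are not taken for onward care. The Follow-up section says that dates of village-clinic re-attendances, facility attendances and hospitalizations are abstracted, along with the follow-up visits scheduled at the index visit.

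**The concern.** The HSA's referral decision is the primary outcome and is what the App is meant to change. Two other main outcomes depend on it.

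First, a caregiver who would go to the health centre in any case is counted as a self-referral if the child was not referred and as a completed referral if the child was. More referral moves the same trip from one label to the other.

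Second, referral directs the child's next contact to a higher-level facility. If the caregiver goes there instead of returning to the village clinic, the contact leaves the re-consultation count even though it took place.

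At stake is the reading of a main outcome. A fall in "Re-consultations at village clinics due to deterioration of illness" may mean that fewer children stayed unwell, or that the same children were seen elsewhere. No listed outcome separates the two, because none counts further contact at all levels together. The primary referral outcome is not affected.

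**Working it through.** **Step 1. The protocol's own figure (Sample size).** At the midpoints of its ranges:

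- control referrals: 4000 × 1% = 40
- App referrals: 4000 × 7.5% = 300
- under-referred in control: 4000 × 6.5% = 260
- sum: 40 + 300 + 260 = 600, which matches the stated figure of about 600.

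So the plan itself implies that about 260 children per 4000 would change from not referred to referred.

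**Step 2. Relabelling, with care-seeking held fixed.** Let s be the share of children needing referral who would present at a facility whether referred or not. The documents give no value, so s is an assumption. Take 8% as needing referral (the article's consensus referral rate): 4000 × 8% = 320 children. Those not referred number 320 − 40 = 280 in control and 320 − 300 = 20 with the App. Self-referrals are 280s and 20s, so the fall is 260s. Total facility presentations are 320s in both phases.

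| s (assumed) | Self-referrals, control → App | Fall | All facility presentations, both phases |
|---|---|---|---|
| 0.10 | 28 → 2 | 26 | 32 (0.8%) |
| 0.25 | 70 → 5 | 65 | 80 (2.0%) |
| 0.50 | 140 → 10 | 130 | 160 (4.0%) |
| 0.75 | 210 → 15 | 195 | 240 (6.0%) |

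Within this group the relative fall is 260/280 = 93%. Self-referral among the other children dilutes it. With an assumed 2% among them, the counts go from 102 to 76 (s = 0.10) up to 284 to 89 (s = 0.75).

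**Step 3. Displacement of village-clinic re-consultations.** Let r be the share of the 260 who would have returned to the village clinic because of deterioration (assumed), and c the share of referrals completed. If each completed referral replaces such a return, the count falls by 260 × r × c. The Background's figure on non-completion makes c = 0.5 a ceiling.

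| r (assumed) | 260 × r × 0.5 | Points of 4000 visits |
|---|---|---|
| 0.10 | 13 | 0.33 |
| 0.20 | 26 | 0.65 |
| 0.30 | 39 | 0.98 |
| 0.60 | 78 | 1.95 |

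The result scales with c. At c = 0.25 each figure halves, and near c = 0 almost nothing moves.

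**Step 4. What the listed outcomes can recover.** Completed referrals plus self-referrals give all facility presentations, so relabelling can be undone by adding them. That sum omits unscheduled village-clinic returns, so it does not show whether further contact at all levels fell.

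**Step 5. Does an all-level count avoid the problem?** Only in part, because a completed referral is itself a contact. Suppose 20% of the 260 would go to a facility unreferred and 20% would return to the village clinic. At most 52 + 52 = 104 then make contact if not referred. If all 260 are referred and 50% complete, at least 130 do. The all-level count rises by at least 26 because caregivers followed advice.

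**The case against.** The strongest case against has five parts.

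1. **Self-referral is not called a success.** The hypothesis and the Discussion name only referral, re-consultation and hospitalization. Completed referral and self-referral are listed side by side, so relabelling would be visible. This stands. A reader might infer that the trial would count fewer self-referrals as a benefit, but no section says so.

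2. **The Discussion is guarded.** It asks for lower hospitalization as well and says only "higher urgent referral rates and reduced re-consultation and hospitalization rates compared to paper-CCM may suggest". This stands, and hospitalization gives some protection. It does not make the village-clinic count interpretable on its own.

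3. **The fall may be real.** Re-consultation counts only when illness deteriorates, and earlier care at a higher level could prevent that. This stands. A reader might infer that both outcomes must fall without any benefit. The documents do not support that: displacement needs completed referrals, and part of any fall could be the intended effect. The point is only that the outcome cannot tell the two apart.

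4. **The displacement is small beside the 6–7 point change in the Sample size section.** The illustrated 0.33–1.95 points are well below it. But that figure is a planning value for HSA-level power, not a threshold below which a change would go unreported.

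5. **Derived outcomes belong in the statistical analysis plan, which is not shown.** This is fair as to where the remedy goes, and a missing composite is not itself the fault. The definitions and the intended reading are, however, fixed in the article.

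**Conclusion.** The concern holds in a limited form. Because re-consultation is counted by place and referral is expected to rise to 7–8%, the village-clinic count can fall partly through displacement. Such a fall alone does not show that re-consultation was prevented. Self-referral can fall by relabelling, which the protocol does not present as a benefit.

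The size of either effect is unknown. The illustrations (26–195 relabelled presentations; 13–78 displaced visits per 4000) use the protocol's 260 under-referred children, but s and r are assumed and 50% completion is a ceiling. The documents do not establish that the App brings no benefit or that a fall is automatic. This is a cheap improvement to interpretation and does not challenge the primary outcome.

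**What to change.** In the statistical analysis plan, which the article says will be public before analysis, add two outcomes. Derive both over all index visits from the visit dates and sites already abstracted:

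- **(a)** any presentation to a higher-level facility within 7 days, regardless of the index referral decision;
- **(b)** any unscheduled contact at any level within 7 days, using the abstracted follow-up schedule to remove planned returns. State that a completed referral visit counts, and show it as a separate component.

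Treat self-referral, completed referral and village-clinic re-consultation as descriptive components. Do not conclude from the village-clinic count alone that re-consultations were prevented; read it with (a), (b) and hospitalization.

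The cost is wording and two derived variables, with no new data collection. The downside, shown in Step 5, is that (a) and (b) may rise simply because caregivers follow referral advice. The plan should say that such a rise is not in itself evidence against the App.
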